### Follow-Up

After the study, the participants will resume their original life in unsupervised mode, but they will need to record daily exercise or physical activity information and send this information to the researchers by email every day. The researchers will gather the participants once a week to discuss CFS-related issues and detailed follow-up actions. They will also give gifts such as traditional Chinese medicine sachets, exercise clothing, and pain patches to thank the participants and increase their enthusiasm for follow-up. All indicators will be reassessed at 8 weeks after the end of the trial to determine the long-term efficacy.

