**Methods:**

We will conduct a randomized, analyst-blinded, parallel-controlled trial with a 12-week intervention and 8-week follow-up. A total of 208 patients of age 20-60 years will be recruited. The patients will be randomly divided into a PLWNT Qigong exercise group (PLWNT Group) and a control group treated with cognitive behavioral therapy at a ratio of 1:1. Participants from the treatment groups will be taught by a highly qualified professor at the Shanghai University of Traditional Chinese Medicine once a week and will be supervised via web during the remaining 6 days at home, over 12 consecutive weeks. The primary outcome will be the Multidimensional Fatigue Inventory 20, while the secondary outcomes include the Pittsburgh Sleep Quality Index, Gastrointestinal Symptom Rating Scale, Hospital Anxiety and Depression Scale, functional magnetic resonance imaging, gut microbiota, and peripheral blood.

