#### Inclusion Criteria

The study inclusion criteria are as follows: (1) age between 20 and 60 years; male or female; (2) severe chronic fatigue lasting at least 3 months, unexplained after clinical evaluation, not caused by work performed during the trial, and unable to be alleviated after rest; (3) meet the criteria of debilitating fatigue worsened by activity, postexertional malaise, cognitive difficulties, and unresolved fatigue upon awakening from sleep; (4) normal blood, urine, liver, and kidney functions; and (5) participants were not taking any other medication for 1 month prior to enrollment in this study and were not on any other treatment regimen.

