#### CBT Group

Qualified CBT therapists with professionally accredited qualifications will be invited to conduct CBT for 1 h each week by giving lectures or psychological consultations on the prevention and treatment of CFS. The sessions will cover CFS diagnosis, diet and nutrition, life management, health and lifestyle changes, physical and mental health education, and medical management. On the remaining 6 days of the week, all participants will be required to listen to lectures on WeChat for 30 minutes every day. If some participants find this inconvenient, they will be allowed to learn at their own pace using the PowerPoint (Microsoft Corp) presentations provided. Each participant will be asked to write down their feelings in a practice recording notebook after each web-based session to ensure that the other conditions are the same as those of the PLWNT group. The entire practice process will last for 12 weeks. Detailed information is available in a previously published paper [39,50]; however, in this research, we will focus on CBT treatment in the gastrointestinal and nervous system fields.

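### Week 20 is to be read as long-term efficacy after unsupervised life, but weekly CFS meetings and gifts mean it measures the effect under continued contact

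*Protocol article*

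**What the plan says.** The abstract describes a "parallel-controlled trial with a 12-week intervention and 8-week follow-up". The Follow-Up section says that "the participants will resume their original life in unsupervised mode" once the intervention is over. Participants must, however, send the researchers activity information by email every day. The section continues: "The researchers will gather the participants once a week to discuss CFS-related issues and detailed follow-up actions". It adds: "They will also give gifts such as traditional Chinese medicine sachets, exercise clothing, and pain patches to thank the participants", with the further aim to "increase their enthusiasm for follow-up". All indicators are then reassessed 8 weeks after the intervention, and that assessment is meant to establish long-term efficacy.

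The CBT Group section describes the control treatment as one hour a week of "giving lectures or psychological consultations on the prevention and treatment of CFS", plus 30 minutes of lectures on each of the other six days.

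The Primary Outcome section lists MFI-20 at weeks 0, 4, 8 and 12. Week 20 appears in Table 1 and in the Follow-Up section.

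**The concern.** A reader of the results would take long-term efficacy after an unsupervised period to mean that the benefit lasted once trial support was withdrawn. Support is not withdrawn under this plan. Researchers stay in weekly contact, and CFS is the subject of the meetings. Participants also receive items that may affect symptoms (sachets, pain patches) or activity (exercise clothing).

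Two readings of week 20 are at stake:

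- **Persistence within an arm.** A score that holds from week 12 to week 20 could reflect a lasting effect of PLWNT, the continued contact, or both.
- **The difference between arms.** The CBT arm continues with something close in topic to its own treatment. The PLWNT arm newly receives it. Equal delivery does not make the meetings neutral, because their content resembles one arm's treatment and not the other's. The likely consequence is a smaller difference.

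The questionnaires at week 20 include self-rated scales completed by patients who know their treatment, so attention and gifts can influence the answers.

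**Working it through.** **1. The Follow-Up section against itself.**

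| Feature | What the section plans |
|---|---|
| Stated condition | Ordinary life without supervision |
| Reporting | Daily email to the researchers |
| Meetings | Weekly, led by researchers, about CFS |
| Gifts | Sachets, exercise clothing, pain patches, given partly to sustain follow-up |
| Stated use of week 20 | Long-term efficacy |

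The first row cannot be squared with the next two. The last row depends on the first.

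**2. Amount of contact.** One meeting a week over 8 weeks gives about 8 meetings.

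- Against the control arm's weekly sessions alone: 8/12 = 67%.
- Against the whole control schedule: 12 × 1 h + 12 × 6 × 0.5 h = 12 h + 36 h = 48 h. The length of a follow-up meeting is not stated. If it were 1 h, the share would be 8/48 = 17%.

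The second figure is the fairer one for total exposure, and it rests on an assumed duration.

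**3. The plan's own sample size.** Inputs from Sample Size Calculation: difference 1.634, SD 3.238, dropout 20%, 104 per group. Statistical Analysis gives two-sided 0.05. Power is not stated in the text available; 90% is assumed.

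- n per group = 2 × (1.960 + 1.282)² × (3.238/1.634)² ≈ 82.5, rounded up to 83.
- 83/0.80 = 103.75, rounded up to 104, which matches.

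Two-sided 0.05/3 with 80% power also gives 83 and then 104, so the 90% is not established.

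**4. What dilution would do (illustration only).** Take 83 completers per group, two-sided 0.05, and the planned difference of 1.634 carried to week 20. Power ≈ Φ(f × (1.634/3.238) × √(83/2) − 1.960), where f is the fraction of the difference that remains.

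| f | Power |
|---|---|
| 1.00 | 0.90 |
| 0.75 | 0.68 |
| 0.50 | 0.37 |
| 0.25 | 0.13 |

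No value of f can be taken from the document, and the document does not tie the 1.634 to week 20. The table shows how sensitive a week 20 comparison would be, not what will happen. The point in step 1 does not depend on it.

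**The case against.** The strongest reply is that the meetings and gifts are described for the participants as a whole. With the same follow-up in both arms, randomization still protects the week 20 comparison. Bias between arms would need unequal delivery or uptake, and the document states neither. This stands. A reader might infer that week 20 can show nothing about PLWNT versus CBT; the text does not support that.

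Several further inferences also go too far:

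- **Mixing of arms.** The section does not separate the arms, but it does not say that they meet together either. An article may leave that detail to the full protocol.
- **Gifts used before week 20.** No date is given. The aim to "increase their enthusiasm for follow-up" suggests early delivery, but their contents and use are unknown. Ethical Considerations mentions free Tai Chi clothing when the study ends, and that timing is itself ambiguous.
- **Breach of eligibility.** The inclusion criterion that participants "were not on any other treatment regimen" is a condition at entry. It does not govern weeks 12 to 20, so the gifts do not contradict it.
- **Meetings as two-thirds of the control treatment.** That ratio leaves out the daily lectures. The meetings are also led by researchers, with no CBT therapist mentioned.

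One practical objection also has weight. Recruitment began in July 2022, so changing follow-up now would place participants under two procedures, and fewer meetings could cost retention in a trial that allows for 20% dropout.

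None of this removes the contradiction in the Follow-Up section, or makes week 20 a measure of what lasts after support ends.

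**Conclusion.** The concern holds in a limited form. The plan describes follow-up as unsupervised while scheduling daily reporting and about eight researcher-led CFS meetings, and it draws a long-term efficacy conclusion from week 20 that these conditions do not support.

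If delivery is equal by arm, week 20 validly estimates PLWNT versus CBT, each followed by continued support. That difference may be diluted. Persistence after withdrawal of support is not measured, and the change from week 12 to week 20 cannot be separated from the contact. The week 12 result is untouched.

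The size of any dilution is unknown. The power figures above rest on an assumed fraction, an assumed 90% starting power, and the planned difference carried to week 20. They should not be quoted as an expected loss.

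**What to change.** 1. Rewrite the Follow-Up section so that its description of the period agrees with the contact planned in it.
2. For participants still to be followed, hold any meetings separately by arm, in identical format, limited to data collection and retention.
3. Give the same neutral gifts to both arms, only after the week 20 assessment.
4. Record meeting attendance and any use of gifts, and note which participants were followed before the change.
5. Report week 20 as the effect of PLWNT versus CBT under continued contact, not as long-term efficacy without support.

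Items 1 and 5 are changes of wording. Item 4 adds a short record. Items 2 and 3 cost little, but they may lower retention slightly, which a gift on completing week 20 would partly offset. They also bring a mid-trial change of procedure. It must apply to both arms alike, so that it does not bias the comparison between them. For participants who have already completed follow-up, only the recording and the reporting can still be put right.

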### Ethical Considerations

This study will be conducted in accordance with the Declaration of Helsinki and the International Code of Ethics for Biomedical Research Involving Human Subjects. The study was approved in March 2022 by the Ethics Committee of Shanghai Municipal Hospital of Traditional Chinese Medicine (Ethics Approval Number 2022SHL-KY-05) and registered in the China Clinical Trials Registry (ChiCTR2200061229). Informed consent will be obtained before enrollment. Before consent seeking, we will introduce the study and explain its purpose. The study data will be anonymized. At the end of the study, A set of Tai Chi clothing for practicing Qigong is provided for free.

## Results

The study was approved in March 2022 by the ethics committee of Shanghai Municipal Hospital of Traditional Chinese Medicine (Ethics Approval Number 2022SHL-KY-05). Recruitment started in July 2022. The intervention is scheduled to be completed in December 2024. Data collection will be completed by the end of January 2025. Over the 3-year recruitment period, 208 participants will be recruited. Data management is still in progress; therefore, data analysis has yet to be performed.

## Discussion

CFS is a complex multisystem disease with unknown etiology. Compared with healthy individuals, individuals with CFS exhibit altered emotion regulation, somatic and sensory processing, and motor control activities [58]. Recommended drug therapy can only partially relieve fatigue and may aggravate other symptoms. Qigong therapy is a mild, low-intensity, mind-body aerobic exercise that emphasizes a combination of physical posture, breathing concentration, and mental concentration, which is a relatively safe and more effective treatment for CFS than other treatments [59]. In recent years, increasing research has been conducted on Qigong for the improvement of the digestive system, endocrine system, and so on [60,61]. Therefore, the aim of this study is to evaluate the efficacy of PLWNT on fatigue, insomnia, anxiety, and gastrointestinal symptoms in patients with CFS and fully explore the mechanisms of brain-gut regulation in the context of CFS.

PLWNT includes several physical and mental exercise methods. The National Institutes of Health considers it a mobile meditation. The abdominal technique included in PLWNT involves the use of meridians and collaterals to regulate organs [62]. The whole process directly massages and stretches the internal organs to stimulate the nerve receptors on the gastrointestinal and mesentery. The PLWNT also focuses on the influence of the direction of the abdomen on the inherent movement of the large and small intestines, stimulates the nerve conduction pathway and the nerve-emotion pathway, and strengthens the connection between the digestive system and the cranial nerves to improve the sleep and gastrointestinal symptoms of patients with CFS, with the help of the heat of friction between the palms, it warms the spleen and yang, assists the righteous qi, promotes the circulation of qi and blood in the whole body, strengthens the interaction between the brain and the intestines, enhances the static strength of muscles, coordinates the autonomic nervous system, and increases blood circulation to the heart, which alleviates fatigue and sleep disturbance and improves the quality of life of patients with CFS [63,64]. In our previous study, PLWNT was found to alleviate fatigue and improve the quality of life of patients with CFS [39]. However, to date, there has been no study on the regulation of CFS fatigue, insomnia, anxiety, and gastrointestinal symptoms by PLWNT Qigong from the perspective of brain-gut regulation.

Regarding the brain-gut regulation mechanism of PLWNT intervention in CFS, various hypotheses have been proposed to explain the interaction between the gut and brain, but special attention has been paid to imaging of neuropeptides, inflammatory mediators, intestinal microbiota, and brain function [65,66]. Increasing evidence shows that the diversity of intestinal flora is essential not only for the health of the intestine but also for the general physiological functions of other organs, especially the brain [67,68]. A recent study found differences in the composition and function of the gut microbiota between patients with CFS and healthy controls [69,70]. In addition, previous fMRI studies have confirmed that the brain network structure and connectivity of patients with CFS are abnormal [71,72] and the changes in the composition profile of the intestinal flora are related to changes in the cingulate and cerebellum signals involved in brain activity [73]. Several studies related to the influence of Qigong exercise on the structural characteristics of intestinal flora have shown that Qigong can substantially increase the diversity of intestinal flora and the content of beneficial bacteria [74,75]. Qigong can also relieve sleep, anxiety, and depression symptoms, while its beneficial effect on gastrointestinal function may be related to brain function connection and central nervous brain area response [76]. Combining neuroimaging and intestinal microbiology analysis, exploring the brain-gut regulation mechanism of CFS treatment represents a novel research direction In this study, we will use fMRI to analyze the functional connectivity density of patients with CFS and its relationship with intestinal flora to explore changes in brain and bowel activity. In addition, the MFI-20, PSQI, HADS, and GSRS will be used to explore the changes in fatigue, sleep, mental, and gastrointestinal symptoms before and after PLWNT intervention. The benefits of PLWNT have been reported previously; however, most studies only assessed self-reported symptoms by patients. Therefore, in this study, we aimed to explore the efficacy and safety of PLWNT for treating CFS from the objective perspective of brain-gut regulation, with the aim of providing high-quality treatment options and optimized guidance for patients with CFS.

## Abbreviations

AE: adverse event
CBT: cognitive behavioral therapy
CFS: Chronic fatigue syndrome
CONSORT: Consolidated Standards of Reporting Trials
FA: flip angle
fMRI: functional magnetic resonance imaging
FOV: field of view
GSRS: Gastrointestinal Symptom Rating Scale
HADS: Hospital Anxiety and Depression Scale
MFI-20: Multidimensional Fatigue Inventory 20
PLWNT: prolong life with nine turn
PSQI: Pittsburgh Sleep Quality Index
SPIRIT: Standard Protocol Items: Recommendations for Intervention Trials
STRICTA: Standards for Reporting Interventions in Clinical Trials of Acupuncture
TE: echo time
TR: repetition time
